#### **11.2.9. Causal relationship**

Medical judgment should be used to determine the relationship, considering all relevant factors, including pattern of reaction, temporal relationship, de-challenge or re-challenge, confounding factors such as concomitant medication, concomitant diseases and relevant history. Assessment of causal relationship should be recorded in the case report forms.

- Yes: There is a reasonable causal relationship between the investigational drug administered and the AE.

- No: There is no reasonable causal relationship between the investigational drug administered and the AE.
- In case of multiples drugs, the causal relationship must be provided by the investigator for all potential trial drugs, i.e. for all other trial drugs.

### 11.3. SERIOUS ADVERSE EVENT AND NEW INFORMATION NOTIFICATION (RESPONSIBILITY OF THE INVESTIGATOR)

Serious adverse events will be reported by the investigator in the patient's CRF and will be followed up until complete resolution.

The investigator will notify the Vigilance Unit without delay about any serious adverse events or new events occurring:

- From the date of the informed consent is signed,
- During the whole patient treatment period as defined by the research,
- Until 90 days after the last dose of study drugs or the initiation of new anti-cancer therapy, whichever is earlier,
- Beyond this period of time, only those SAEs suspected to be related to the study treatment or the research (diagnostic procedures, examinations carried out during the research ...) will be collected without any limitation in terms of deadline. Nonetheless, the Sponsor will evaluate any safety information related to the clinical trial that is spontaneously reported by an Investigator beyond the time frame specified in the protocol.

| Type of Event                                         | Reporting procedure                                            | Deadline for reporting to the sponsor     |
|-------------------------------------------------------|----------------------------------------------------------------|-------------------------------------------|
| SAE                                                   | SAE Notification form + written report form if necessary       | To be reported immediately to the sponsor |
| New information                                       | Written report form                                            | To be reported immediately to the sponsor |
| Pregnancy                                             | Pregnancy Notification form + Written report form if necessary | As soon as pregnancy is confirmed         |
| Special considerations and events of special interest | SAE Notification form                                          | To be reported immediately to the sponsor |

The investigator must complete the "Serious Adverse Event Notification Form" (Appendix 5) immediately, in English, and assess the relationship with the study treatment. The form must then be dated, signed and sent by fax to the following address without delay to:

|                                                                                                                                                                                                                                                                               |
|-------------------------------------------------------------------------------------------------------------------------------------------------------------------------------------------------------------------------------------------------------------------------------|
| 
CELLULE DE VIGILANCE (VIGILANCE UNIT) – R&D UNICANCER
 
[contact]
 
Or contact : R&D Unicancer – Mail : pv-R&[contact]
 |
|-------------------------------------------------------------------------------------------------------------------------------------------------------------------------------------------------------------------------------------------------------------------------------|

For each event, the investigator will record:

- A description of the event that is as clearly as possible, using medical terminology,
- The date AE met criteria for serious AE,
- The seriousness criteria,
- The date of hospitalization and the date of discharge,
- The probable cause of death and the date of death if appropriate,
- The date the event started and ended,
- The patient's relevant medical history,
- The steps taken and whether or not corrective treatment was required, whether or not the investigational treatment was discontinued, etc.
- Concomitant medications / therapies
- The causal link between this event and the study treatment, disease treated or an intercurrent disease or treatment, or any obligation imposed by the research (a treatment-free period, additional examinations requested as part of the research etc.),

- Clinical course. If the event was not fatal, it should be monitored until recovery, until the patient has returned to his/her previous condition, or until any sequelae have stabilized,  
- Whenever possible, the investigator must also attach the following with the serious adverse event report:

- A copy of the hospitalization or extended hospitalization report,
- A copy of the autopsy report, if required,
- A copy of all the results of any additional tests performed, including relevant negative results, along with the normal laboratory values,
- Any other document he or she considers useful and relevant.

All these documents must be anonymized. Additional information may be requested (by fax, by telephone or during a visit) by the CRA and/or by the Vigilance Unit using a follow-up request form.

The investigator is responsible for providing appropriate medical follow-up for patients until resolution or stabilization of the adverse event or until the patient's death. Sometimes this may mean that follow-up will extend beyond the patient's withdrawal from the trial.

The investigator keeps the documents about the presumed adverse effect so that the information previously sent can be added to if necessary.

The investigator responds to requests for additional information from the Vigilance Unit in order to document the original observation.

#### 11.4. EVENTS OF SPECIAL INTEREST

Potential drug-induced liver injury (DILI) are considered important medical events and should be reported as SAEs.

Patients with transaminase increase and/or alkaline phosphatase (AP)/gamma-glutamyl transpeptidase (GGT) increased with or without total bilirubin (TBIL) increase may be indicative of potential drug-induced liver injury (DILI).

The threshold for potential DILI may depend on the patient's baseline AST/ALT and TBIL values; patients meeting any of the following criteria will require further follow-up as outlined below:

- For patients with normal ALT and AST and TBIL value at baseline: AST or ALT > 3.0 x ULN and with TBIL > 2.0 x ULN
- For patients with elevated AST or ALT or TBIL value at baseline: AST or ALT > 2 x baseline and > 3.0 x ULN and TBIL > 2 x baseline and > 2.0 x ULN

Medical review needs to ensure that liver test elevations are not caused by cytolysis and/or cholestasis due to other causes, especially liver progression.

The evaluation should include laboratory tests, detailed history, physical assessment and the possibility of liver metastasis or new liver lesions, obstructions/compressions.

All cases confirmed with no other alternative cause for liver function test abnormalities identified should be reported as SAE. All events should be followed up with the outcome clearly documented.

For management of hepatic toxicity, refer to appendix 8.

For more information, refer to FDA's guidance document:

<https://www.fda.gov/downloads/Drugs/Guidance/UCM174090.pdf>.

Skin rash grade  $\geq 3$ , associated or not with fever, are considered important medical events and should be reported as SAEs (see section 11.3).

#### 11.5. REPORTING PREGNANCY CASES OCCURRED WITHIN THE CLINICAL TRIAL

If a patient becomes pregnant during the course of the study, study drugs should be discontinued immediately.

The outcome of any conception occurring from the date of the first dose until 3 months after the last dose should be followed up and documented.

Pregnancy itself is not regarded as an adverse event unless there is a suspicion that the investigational product under study may have interfered with the effectiveness of a contraceptive medication. Congenital abnormalities/birth defects and spontaneous miscarriages should be reported and handled as SAEs. Elective abortions without complications should not be handled as AEs. The outcome of all

pregnancies (spontaneous miscarriage, elective termination, ectopic pregnancy, normal birth or congenital abnormality) should be followed up and documented even if the patient was withdrawn from the study.

If any pregnancy occurs in the course of the study, then Investigators or other site personnel must inform Sponsor within one day i.e., immediately but no later than the end of the next business day of when he or she becomes aware of it. Any pregnancy, suspected pregnancy, or positive pregnancy test must be reported to the Vigilance Unit immediately by facsimile using the Pregnancy Report form (appendix 6).

Paternal exposure: Male patients should refrain from fathering a child for 4 months (120 days) following the last dose or donating sperm during the study and for 4 months following the last dose.

Pregnancy of the patient's partners is not considered to be an adverse event. However, the outcome of all pregnancies (spontaneous miscarriage, elective termination, ectopic pregnancy, normal birth or congenital abnormality) should if possible be followed up and documented.

The outcome of any conception occurring from the date of the first dose until 7 months after the last dose should be followed up and documented.

In the case of pregnancy of the female partner of a trial patient, the Investigator will obtain her consent to provide the information in these situations.

The Investigator will follow the pregnancy until its outcome, and must notify the Vigilance Unit the outcome of the pregnancy within 24 hours of first knowledge as a follow-up to the initial report.

For any event during the pregnancy which meets a seriousness criterion (including fetal or neonatal death or congenital anomaly) the Investigator will also follow the procedures for reporting SAEs (complete and send the SAE form to the Vigilance Unit by facsimile within 24 hours of the Investigator's knowledge of the event).

All neonatal deaths that occur within 30 days of birth should be reported, without regard to causality, as SAEs. In addition, any infant death at any time thereafter that the Investigator suspects is related to the exposure to the study drug/IMP should also be reported to the Vigilance Unit by facsimile within 24 hours of the Investigators' knowledge of the event.

Whenever possible, the investigator must also attach the following with the serious adverse event report:

- A copy of the hospitalization or extended hospitalization report,
- A copy of the autopsy report, if required,
- A copy of all the results of any additional tests performed, including relevant negative results, along with the normal laboratory values,
- Any other document he or she considers useful and relevant.

All these documents must be anonymized.

Additional information may be requested (by fax, by telephone or during a visit) by the Vigilance Unit.

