  13. Women of childbearing potential must have a negative serum pregnancy test within 72 hours prior to receiving the first dose of study medication.
  14. Both women and men must agree to use an highly effective method of contraception throughout the treatment period and for seven months (210 days) in WOCBP or four months (120 days) in men sexually active with WOCBP after discontinuation of treatment. Acceptable methods for contraception are described in section 7.4.1.
  15. Voluntary signed and dated written informed consents prior to any specific study procedure,
  16. Patients with a social security in compliance with the French law.
  17. Documented disease progression (as per RECIST v1.1) before study entry.
    - For patient of cohorts E (STS) and cohort I (Solid tumors - TLS+): this progression will be confirmed by central review on the basis of two CT scan or MRI obtained at less than 6 months in the period of 12 months prior to inclusion.
    - For patient of cohort F (RR-DTC) : this progression will be confirmed by central review on the basis of two CT scan or MRI obtained at less than 12 months prior to inclusion.
  18. Cancelled (MSA6)
  19. For patients with non-small cell lung cancer (cohort H):

- Subjects with histologically or cytologically confirmed diagnosis of non-squamous NSCLC
  - Documented disease progression based on radiographic imaging, during or after a maximum of 2 lines of systemic treatment for locally/regionally advanced recurrent, Stage IIIb/Stage IV or metastatic disease. Two components of treatment must have been received in the same line or as separate lines of therapy
    - A maximum of 1 line of platinum-containing chemotherapy regimen in the metastatic setting, and
    - A maximum of 1 line of PD(L)1 mAb containing regimen, and
    - Patients must have received at least 4 months of PD(L1) mAb treatment.
  - No EGFR, ALK, ROS1 positive tumor mutations
  - Subjects with known BRAF molecular alterations must have had disease progression after receiving the locally available SoC treatment for the molecular alteration.
20. For patients with urothelial cancer (cohort J):
- A maximum of 1 line of PD(L)1 mAb containing regimen, and
  - Patients must have received at least 4 months of PD(L1) mAb treatment.
21. For HPV-associated cancer (cohort K), TMB-high solid tumors (cohort M) MSI-high solid tumors (cohort N), Non clear-cell renal carcinoma (cohort O):
- A maximum of 1 line of PD(L)1 mAb containing regimen, and

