## **7.4. RESTRICTION DURING THE STUDY**

### **7.4.1.Contraception**

Women of childbearing potential must be informed that Regorafenib may cause foetal harm. Women of childbearing potential (WOCBP) and their partners should ensure highly effective contraception during treatment and for 7 months (210 days) in WOCBP or 4 months (120 days) in men sexually active with WOCBP after last dose of study drug(s).

Males, who are sexually active, must agree to the use of an highly effective method of contraception throughout the period of taking study treatment and for at least 4 months (120 days) after last dose of study drug.

The following restrictions apply while the patient is receiving study treatment and for the specified times before and after:

– **Female patient of child-bearing potential:**

Females of childbearing potential who are sexually active with a non-sterilized male partner must use at least 1 **highly** effective method of contraception (table below) from the time of screening and must agree to continue using such precautions for 7 months (210 days) after the last dose of study treatment. Non-sterilised male partners of a female patient must use male condom plus spermicide throughout this period. Not engaging in sexual activity for the total duration of the drug treatment and the drug washout period is an acceptable practice; however, periodic abstinence, the rhythm method, and the withdrawal method are not acceptable methods of birth control. Female patients should also refrain from breastfeeding throughout this period.

– **Male patients with a female partner of childbearing potential:**

- Non-sterilized males who are sexually active with a female partner of childbearing potential must use a male condom plus spermicide from screening through 4 months (120 days) after receipt of the final dose of study treatment. Not engaging in sexual activity is an acceptable practice; however, occasional abstinence, the rhythm method, and the withdrawal method are not acceptable methods of contraception. Male patients should refrain from sperm donation throughout this period.
- Female partners (of childbearing potential) of male patients must also use a highly effective method of contraception throughout this period (Table below).

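### Section 11.5 gives two conflicting follow-up windows for conceptions (3 and 7 months after the last dose), and by position the shorter one falls on female patients, whose contraception period is 7 months

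*Protocol*

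**What the plan says.** Section 11.5 (pregnancy reporting) opens with the case of a patient who becomes pregnant. The next sentence requires follow-up and documentation of the "outcome of any conception occurring from the date of the first dose until 3 months after the last dose". Further down, after the heading on paternal exposure and between the sentences on partners' pregnancies and on the partner's consent, it requires the same for the "outcome of any conception occurring from the date of the first dose until 7 months after the last dose". Apart from the number of months the wording is identical, and neither sentence says whether it concerns patients, partners or both.

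The at-risk periods are set elsewhere, by sex. Section 7.4.1 says that female patients of childbearing potential "must agree to continue using such precautions for 7 months (210 days) after the last dose of study treatment". Inclusion criterion 14 (section 4.1) gives both periods: "seven months (210 days) in WOCBP or four months (120 days) in men sexually active with WOCBP". Section 11.5 repeats the male period: "Male patients should refrain from fathering a child for 4 months (120 days) following the last dose".

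Three further rules bear on the point:

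- Section 11.2.8 requires exposure during pregnancy to be reported in every case, and it includes a woman who becomes pregnant after stopping the product.
- The reporting table in section 11.3 asks for notification once a pregnancy is confirmed.
- Section 11.5 itself asks for the outcome of all pregnancies to be followed, even in patients who have been withdrawn.

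None of these sets a limit after the last dose.

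**The concern.** Two different limits for the same item cannot both be the rule. A site has to decide which sentence governs which patient, and position in the text is the natural guide. Position pairs the limits with the groups the wrong way round: the shorter collection window goes to the group with the longer at-risk period, and the longer window to the group with the shorter one.

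What is at stake is safety data on maternal exposure, for a drug that section 7.4.1 says may harm the foetus. Pregnancies will be few, but each is a reportable event, and uneven collection between sites would leave the trial unable to say whether its pregnancy outcomes are complete. No efficacy endpoint, sample size or error rate is touched.

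**Working it through.** The plan states no figure to reproduce, so the check compares time windows. The protocol equates 7 months with 210 days and 4 months with 120 days, which is 30 days per month. On that convention 3 months is 90 days.

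| Group | At-risk period after last dose (7.4.1; criterion 14; 11.5) | Window in 11.5, by position | Window minus at-risk period |
|---|---|---|---|
| Female patients | 210 days | 90 days | 90 − 210 = −120 days |
| Partners of male patients | 120 days | 210 days | 210 − 120 = +90 days |

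**Reading by position.** For female patients, 120 of 210 days (4/7, about 57%) lie outside the window, namely months 4 to 7. For partners, collection runs 90 days beyond the male period. That is additional safety information and does no harm.

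**Literal reading.** The 7-month sentence speaks of any conception and so includes those of female patients. Their shortfall is then 210 − 210 = 0 days. The 3-month sentence becomes redundant, but it is still there and still contradicts the other.

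**Do other rules settle the matter?** They help without deciding it.

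- The unlimited rule in section 11.2.8 and the table in section 11.3 govern notification. They do not say which conceptions must be followed to outcome. The two window sentences are the ones that do.
- The unlimited all-pregnancies sentence in section 11.5 does require outcome follow-up. It therefore conflicts with a 3-month limit and does not explain it.
- Section 11.5 treats spontaneous miscarriages and congenital abnormalities as serious adverse events. Under section 11.3, however, general notification of serious events ends 90 days after the last dose, or earlier if new anticancer therapy starts. After that only events suspected to be related to the treatment or the research are collected, without a deadline. A miscarriage in month 5 judged unrelated could therefore fall outside that general rule too.
- The schedule of assessments shows no pregnancy test after the discontinuation visit, so detection in months 4 to 7 depends on the patient's report or on ordinary follow-up contacts.

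**The case against.** The strongest reply is that nothing is actually lost. The 7-month sentence is not restricted to partners, and its length equals the female contraception period and not the male one, so it may well have been meant for female patients. Several rules require pregnancies to be reported or followed with no cut-off after the last dose. Section 11.5 adds reporting within 24 hours for serious events during a pregnancy, including fetal or neonatal death and congenital anomaly, and it requires all neonatal deaths within 30 days of birth to be reported regardless of cause. Related serious events are collected indefinitely. To miss a case, a site would have to apply one sentence and disregard the rest. Contraception is mandatory, so cases will be rare.

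Most of this stands. A reader might infer from the 3-month sentence that maternal conceptions are followed only to 3 months and that those in months 4 to 7 fall outside collection altogether. The documents do not support that, because the 7-month sentence and the unlimited rules can each be read to cover them. Nor do they show that 3 months was deliberately chosen for women; an editing inconsistency is at least as likely.

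What the reply does not remove is the contradiction. The broader rules show that the 3-month sentence sits badly with its surroundings, but they do not tell a site to ignore it.

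**Conclusion.** Section 11.5 contradicts itself on how long conceptions are followed, and by position neither window matches the at-risk period of the group it sits with. The possible loss for female patients ranges from 0 days (the 7-month sentence covers everyone) to 120 of 210 days (the 3-month sentence alone governs them and the unlimited rules are not applied). The 4/7 figure belongs to that upper end only and should not be quoted as the size of an established gap.

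The range assumes 30 days per month, as the protocol's own conversions imply, and takes the contraception periods as the protocol's statement of the at-risk period. The point deserves correction because it lies in an operative safety-collection rule that sites must apply as written. It has no bearing on the efficacy conclusions.

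**What to change.** Reconcile the two sentences in section 11.5 with each other and with section 7.4.1 and inclusion criterion 14. State one explicit window for conceptions in female patients and one for conceptions in partners of male patients, and name the group in each sentence. Neither window should be shorter than the at-risk period the protocol already gives for that group (7 months for female patients, 4 months for male patients). A partner window longer than 4 months can stay if the sponsor wants it.

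It would also help to say in the same place that these windows apply to outcome follow-up whether or not an event is judged related, so that the 90-day limit on general serious-event notification in section 11.3 is not read as cutting them short.

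The contraception periods and all treatment rules are unchanged. The cost is a sentence or two of wording and, at most, a small amount of extra safety follow-up.
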